### 2.9. Study Timelines

The study will fit into approximately two years from the time of the first participants allocation of intervention. The allocation of study timelines has been allocated in three different thematic areas of enrolment, intervention and assessments pre-and post-exposure ttC. The study period will focus on enrolment, allocation of treatment and post allocation. This will be concluded by the close out processes. The allocation of timelines in the study was assisted by the standard protocol items: recommendation for international trails (SPIRIT) timetable shown in the Table 3 below.

Women shall be enrolled in the study as they get pregnant and attend their first ANC to be able to acquire their Mothers passports and get referral to CHWs. Enrolment shall follow the stated criteria through an eligibility assessment. CHWs shall identify as many pregnant women as possible in order for the study eligibility screening to be done so that to attain the required sample. For this study, 1218 participants have to complete the interventions and therefore any drop outs before the 6 weeks after child birth will be replaced by another woman. The anticipated eligibility screening, follow up loss and eventual hitting the targeted number of participants is presented in the Consolidated Standards of Reporting Trials (CONSORT) flowchart in Figure 2 below:

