### 2.4. Study Population

The study population for the quantitative study involves pregnant mothers registered by VHTs on suspecting the pregnancy. The study will follow these participants from pregnancy until six weeks post-delivery. For qualitative data (key informant interviews and focus group discussions), mothers shall be enrolled towards the end of the study period. Enrolment for the qualitative process evaluation will also cover VHTs, health facility staff, district health leaders and staff from the World Vision Uganda office in the department of health. To be included, women have to have either an ANC card with a child health card or a mother-child passport. Participants shall be considered discontinued if they migrate from the location included into the study at any point in time during the community health worker (CHW) follow up period.

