### 2.5. Conceptual Framework

The proposed study aims to determine the effect of ttC on pregnancy outcomes and newborn survival in rural Uganda. Specifically, the study aims to ascertain the extent to which ttC improves uptake of timely goal-oriented ANC with a focus on the recommended visits, and to determine whether ttC contributes to the recommended hygienic birth practices. Additional aims are to establish the extent to which ttC improves essential newborn care practices during the newborn period, and to ascertain the extent to which ttC fosters positive male involvement in pregnancy and newborn care. Finally, the study aims to ascertain the relationship between ttC implementation and appropriate pregnancy weight gain by end of pregnancy and appropriate birth weight.

We expect that if the VHTs implement ttC effectively, there will be an increased uptake of ANC services in the intervention districts, including the timely attendance of goal-oriented ANC services, and the development and implementation of a birth plan. In addition, we expect essential newborn care improvements at the levels of the health facility and the community, aimed at newborn survival within the first 28 days of life, as well as improved visible male involvement in MNH care, including escorting the pregnant women for at least one ANC where couple human immunodeficiency virus (HIV) counselling and testing occurs. Ultimately, we expect these improvements to result in appropriate pregnancy outcomes and newborn survival (see Figure 1).

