### 2.8. Sample Size

The sample size is calculated using the formula for comparing differences in rates and proportions between two groups and determining the number of subjects per group^n^, using an individual binary for a two-sided significant level α and power 1-β [27]. With an anticipated effect size of 10% [δBinary = (^μ^T − ^μ^C)], α = 0.05 (two-sided), β = 0.2,^ z^1^−α^/2 = desired significance level at 95% (0.05). ^Ζ^1 − β = desired power at 80% (0.842), type of test = two-sided, and absolute risk reduction = 10%.

Since the study focuses on uptake of pregnancy services and essential newborn care, the key participants are pregnant mothers. We, therefore, estimate the pregnancy rate from each area using the 2020 population estimates per district, then turning the pregnancy rate into a percentage proportion. To estimate pregnancy rate, the focus will be on the recommended women of reproductive age within the population. Using the health care planning estimation, it is estimated that 24% of the population are women of reproductive age [28]. An estimation of number of births, abortions and foetal losses was acquired from the actual total 2019 health management and information systems [29] reports for both districts. This provided a 1107-sample size in the two districts. This will be increased by 10% to 1218 participants to cater for a non-response. Therefore, the treatment and control groups will each have 609 mothers at the end of the study.

To determine number of clusters needed (n_cluster) [27,30]: n _cluster = total number of participants in the two groups (/fixed cluster size) which is (^n^Cluster_Binary 2)/m = 1218/60, giving us 20 clusters. In order to have the same number of clusters per arm, the number of clusters will be increased to the nearest upper even number, which is 20 in this study. This means that the sample size contains 1218 pregnant mothers in 20 clusters which is the sub-county by the administrative units of Uganda [31].

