No	Variable	Description of Variable	Tool to Be Used
Dependent Variables			
1	Appropriate pregnancy weight gain at end of months pregnancy	Pregnancy weight gain of 11.5 kg to 16 kg by the end of the pregnancy	SQ
2	Newborn morbidity within the first 28 days of life	Newborn morbidity (focusing on cord infections, sepsis, asphyxia, fever, common flu and cold and diarrhea, pneumonia) within the first 28 days of life	SQ and ttCR
3	Appropriate birth weight	Appropriate birth weight of 2.5 kg or more	SQ
4	Mortality of newborns and mothers	If the mother died during pregnancy or childbirth, if the baby died either during pregnancy, childbirth or within the first 28 days of life.	SQ and ttCR
5	Overall maternal wellness	During pregnancy or newborn period, a mother does not develop sepsis, urinary tract infections, obstruction during birth or any danger signs during this period.	SQ and ttCR
Independent Variables			
1	Uptake of timely goal-oriented ANC	With a focus on the recommended four visits, the associated recommended services offered during these visits and timeliness of attendance.	VHTR, SQ and ttCR
2	Clean birthing practices	Birth attended by a skilled health provider, delivery happened in a health facility and a mama kit was used during the process.	SQ and ttCR
3	Essential newborn care practices (ENC) during the newborn period	Early initiation of breastfeeding, cord care practices, baby thermal care, sustained breastfeeding and baby WASH practices.	SQ and ttCR
4	Positive male involvement in pregnancy and newborn care	Man participates in at least one ANC, does an HIV test with the mother, available during birth, supports mother to help her rest, contributes finances for related logistics.	SQ

Notes: SQ: Study questionnaire, ttCR: ttC register, VHTR: Ugandan VHT household register.

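### Replacing women who do not complete to six weeks after birth selects the sample on completion and could remove deaths that are study outcomes

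*Protocol article*

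**What the plan says.** Section 2.9 fixes the target as completers: "1218 participants have to complete the interventions and therefore any drop outs before the 6 weeks after child birth will be replaced". Section 2.8 reaches the same number by adding an allowance to a base of 1107, "This will be increased by 10% to 1218 participants to cater for a non-response", and expects 609 mothers in each group when the study ends. The two sections therefore agree that 1218 is the final count.

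Section 2.4 sets the follow-up, "The study will follow these participants from pregnancy until six weeks post-delivery", and gives the only stated ground for discontinuation: "Participants shall be considered discontinued if they migrate from the location included into the study at any point in time".

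Section 2.5 states the aim: "The proposed study aims to determine the effect of ttC on pregnancy outcomes and newborn survival in rural Uganda". Table 4 accordingly lists mortality among the dependent variables, described as "If the mother died during pregnancy or childbirth, if the baby died either during pregnancy, childbirth or within the first 28 days of life". Every death in that description falls before the six-week cut-off of the replacement rule.

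**The concern.** Completion happens after enrolment. If it decides who counts towards 1218, the final group consists of women who stayed, and a new woman does not supply the outcome of the one who left. If those who leave fare worse, each district's results look better than they are. The comparison between districts is then biased to the extent that loss, or the outcome gap between leavers and stayers, differs between Hoima and Masindi.

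The deaths are the sharper problem. Under Table 1 the last four counselling visits come after birth: three in the first week and one at six weeks. A woman who dies, or whose pregnancy or newborn is lost, cannot receive all of them as planned, so a field team told that participants must complete the interventions could well treat her as a drop-out and replace her. That would take an outcome event out of a study whose stated aim includes newborn survival.

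The districts could differ in this. Section 2.6 describes monthly meetings to keep the intervention's health workers to their visits, and Section 2.7 describes nothing equivalent for control. For mortality, Table 4 names the study questionnaire and the ttC register. Section 2.10 places the ttC registers in Hoima, so a woman replaced in Masindi before the questionnaire may leave no second record among the sources that Table 4 names.

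**Working it through.** **Inputs from the protocol article.** Base 1107, allowance 10%, total 1218, 609 per group, planned difference 10 points (Section 2.8). Neonatal mortality 19 per 1000 live births, a global figure (Background). Infant mortality 43 per 1000 and maternal mortality 336 per 100,000 for Uganda (Abstract and Background). The 1107 is taken as printed: the article does not give the proportions behind it, and this point does not depend on them.

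**Inputs assumed.** Loss before six weeks of 10%, with 5% and 20% as the range. Outcome gap between completers and non-completers of 20 to 40 points. One live birth per woman. The documents give no figure for the first two.

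**1. The plan's own figure.** 1107 × 1.10 = 1217.7, rounded up to 1218; 1218 / 2 = 609. Reproduced.

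**2. What the replacement rule implies.** Women enrolled = 1218 / (1 − loss).

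| Loss (assumed) | Enrolled to reach 1218 completers | Set aside |
|---|---|---|
| 5% | 1283 | 65 |
| 10% | 1354 | 136 |
| 20% | 1523 | 305 |

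The allowance in step 1 and the replacement in step 2 cover the same women twice. Covering loss once, 1107 evaluable women need 1107 / 0.90 = 1230 enrolled (615 per group). Enrolling 1218 and losing 10% leaves 1218 × 0.90 = 1096, which is 11 below 1107.

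**3. Bias in one arm's uptake.** If a fraction d is lost, and completers and non-completers have proportions p_c and p_n, the whole group has (1 − d)p_c + d·p_n. A completers-only estimate is therefore too high by d × (p_c − p_n). With d = 0.10:

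- gap 20 points: 0.10 × 20 = 2 points;
- gap 40 points: 0.10 × 40 = 4 points.

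At 5% loss the range is 1 to 2 points; at 20% it is 4 to 8.

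**4. Bias in the comparison.** This is the difference between the two arms' biases. With equal loss and equal gaps it is zero. With 10% loss in one district and 5% in the other and the same gap, it is 0.05 × 20 to 0.05 × 40, or 1 to 2 points. With 10% loss in one district only, it is the full 2 to 4 points. The direction depends on which district loses more.

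**5. Deaths at stake per arm.**

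- Newborn: 609 × 19/1000 = 11.6, about 12. At the first-year rate, 609 × 43/1000 = 26.2, which is an upper bound for deaths in the first 28 days.
- Maternal: 609 × 336/100,000 = 2.05, about 2.
- Fetal losses come on top; the article prints no rate for them.

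Suppose true mortality is equal, with 12 newborn deaths per arm. If 3 of the 12 in one district are replaced, the observed ratio is 9/12 = 0.75. If half are replaced in one district only, it is 0.5 or 2.0, depending on which district.

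**The case against.** The strongest reply is that the article never calls a death a drop-out. Section 2.4 names migration alone, and Table 4 collects deaths as outcomes, so the two together can be read as treating deaths as endpoints and migrants as drop-outs. That stands to this extent: a reader might infer that deaths will be discarded, or that women who miss visits are certain to be swapped, and the documents support neither. They do leave both open, because Section 2.9 speaks of any drop-out and ties the target to completing the interventions.

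A reader might also infer that the rule conceals attrition. This cannot be judged. Section 2.9 says that Figure 2 presents the loss to follow-up, and that figure is not shown. Nor does the text say that replaced women's data are removed from the analysis. Even so, a count in a flow diagram does not recover outcomes that were not collected.

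A third inference, that Sections 2.8 and 2.9 contradict each other, fails because both treat 1218 as the number at the end. The fault is a duplicated allowance, and the article calls the 10% non-response, not loss.

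Finally, no figure shows that retention differs by district. Control women also have scheduled visits (Table 2), and nothing links migration to counselling. Differential loss is a possibility, and its size here is assumed.

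**Conclusion.** The point holds as a defect in a rule that the article states outright, so it is more than a detail left to an analysis plan. The sample is selected on completion, and nothing protects the maternal, fetal and newborn deaths from replacement although they are dependent variables.

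The size is not known. At the assumed 10% loss and 20 to 40 point gap, one arm's uptake is overstated by 2 to 4 points, a fifth to two fifths of the planned 10-point difference. The comparison carries only the part that differs between districts, which could be nil. Mortality is more fragile: with about 12 newborn deaths per arm, and at most 26, misplacing a few in one district would visibly move the result. That loss of deaths is a risk under the current wording, not an established consequence.

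**What to change.** - Delete the replacement rule from Section 2.9.
- Keep every enrolled woman in her district of enrolment and analyse her however many visits she completed.
- State in Section 2.4 that maternal, fetal and newborn deaths are outcomes and never drop-outs.
- In Sections 2.8 and 2.9, describe the sample as the number enrolled, not the number completing. With the 10% treated as loss, 1107 evaluable women need about 1230 enrolled. If 1218 is kept, state that about 1096 would be evaluable, 11 short of 1107.
- Bring Figure 2 into line with these statements.

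The cost is wording, plus fewer evaluable women than 1218. Recruitment becomes lighter: 1230 is 124 fewer than the 1354 that the present rule needs at 10% loss. Outcomes must still be sought for women who stop receiving visits, which takes some field effort.

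### The plan replaces undefined drop-outs until 1218 women complete the interventions, which permits a completers-only district comparison and conflicts with mortality being an outcome in the same window

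*Protocol article*

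**What the plan says.** Section 2.9 of the protocol article fixes the target as a number of completers: "For this study, 1218 participants have to complete the interventions". It then adds that "any drop outs before the 6 weeks after child birth will be replaced by another woman". Section 2.8 (Sample Size) likewise puts 609 mothers in each group at study end, although its total of 1218 already contains a 10% allowance for non-response.

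Section 2.4 (Study Population) sets the planned observation period: "The study will follow these participants from pregnancy until six weeks post-delivery". It gives one ground for discontinuation: "Participants shall be considered discontinued if they migrate from the location included into the study at any point in time".

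Table 4 lists mortality of newborns and mothers as dependent variable 4, described as "If the mother died during pregnancy or childbirth, if the baby died either during pregnancy, childbirth or within the first 28 days of life". Its sources are the study questionnaire and the ttC register. Section 2.11 says the questionnaire supplies the outcome data when the intervention ends. In Table 4 it is the only source for pregnancy weight gain, birth weight and male involvement.

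**The concern.** A woman's place in the counted cohort depends on what happens after enrolment, namely whether she is still taking part six weeks after birth. In a non-randomised comparison of two districts, that adds selection to whatever confounding already exists. Women who stay to the end are likely to differ from those who leave in settlement, use of services and pregnancy course, and these bear on the study's outcomes.

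Replacement restores the number but not the comparability. A final count of 609 per district would look complete even if the two sets of survivors of the process were no longer alike.

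The rule also touches the stated hypothesis, which includes newborn survival. Every death in Table 4 occurs before six weeks after birth, so it falls inside the replacement window. A woman who dies, or whose pregnancy is lost, cannot complete the visit schedule as specified. Unless the protocol says that such a woman is an outcome and not a drop-out, field staff could replace her in good faith.

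**Working it through.** **1. The plan's own figure.** Section 2.8 gives a base of 1107 and a 10% increase: 1107 × 1.10 = 1217.7, rounded up to 1218, and 1218 / 2 = 609 per district. The figure reproduces, and the 10% is already inside it. Requiring 1218 completers therefore provides for loss twice. Enrolment would have to reach 1218 / (1 − d), where d is the drop-out share (assumed, as none is given):

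| d | women enrolled | beyond 1218 |
|---|---|---|
| 5% | 1283 | 65 |
| 10% | 1354 | 136 |
| 20% | 1523 | 305 |

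**2. The passages side by side.**
- Section 2.9: any drop-out before six weeks after birth is replaced; the term is undefined; completion of the interventions is required of all 1218, hence in both districts.
- Section 2.4: the only stated ground for discontinuation is migration.
- Table 4: maternal death in pregnancy or childbirth, and death of the baby up to day 28, are outcomes.

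If drop-out means migration only, the requirement to complete is wider than the replacement rule it is meant to justify. If drop-out means failure to complete, women with a fatal outcome come under the rule and Table 4 loses its events. The text does not choose between these readings.

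**3. Deaths at stake.** The Background gives 336 maternal deaths per 100,000 live births. Applied to women as an approximation, 609 × 336 / 100,000 = 2.05 per district and 1218 × 336 / 100,000 = 4.09 in all. If deaths were treated as drop-outs, the observed number would be 0. For babies, if a share s of bereaved women were replaced and not counted, the observed risk would be about (1 − s) times the true risk.

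**4. Bias in a completers' comparison when ttC has no effect.** Let p be the true rate in all women, d the share lost and g the gap in points between completers and those lost. Then p = p_completers − d × g, so p_completers = p + d × g. With the same p in both districts:

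spurious difference = d_Hoima × g_Hoima − d_Masindi × g_Masindi

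The 74% skilled attendance at birth is from the Background; every d and g is an assumption.
- Net excess non-completion of 20% in Hoima, gap 25 points: 0.20 × 0.25 = 0.05. With no loss in Masindi this reads 79% against 74%, or +5 points, half of the planned 10-point effect.
- The same excess in Masindi: −5 points.
- Equal loss and equal gap: 0.
- Equal loss of 10% but gaps of 25 and 10 points: 0.025 − 0.010 = +1.5 points.

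A second illustration uses a true rate of 60% in both districts and p_completers = (p − d × r) / (1 − d), where r is the success rate among those lost. Loss of 10% against 5% gives +1.8 points if r = 30% and +3.5 if r = 0. Loss of 15% against 5% gives +3.7 and +7.4.

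**The case against.** Several stronger readings are tempting, and the document does not support them.

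- *Every non-completer is replaced, and deaths leave the cohort.* Section 2.9 replaces drop-outs, not non-completers by name. Section 2.4 names only migration, and Table 4 plans to collect deaths, so treating them as drop-outs would defeat the authors' own outcome. Removal of deaths is an inference from the completion requirement. The inclusion rule ("women have to have either an ANC card with a child health card or a mother-child passport") does not settle it, since the passport route is open and section 3.2 plans to issue cards at first contact.
- *Replaced women's data are discarded.* Nothing says so, and no analysis set is named. Analysis populations are commonly left to the statistical analysis plan, and Figure 2, which is said to show follow-up loss, is not in the text available.
- *The filter acts on Hoima alone.* The requirement covers all 1218 women. Table 2 gives Masindi its own visit schedule, and Table 3 lists control implementation among the interventions. Differential loss is possible but not built in.
- *The bias is known to be large.* It depends wholly on assumed inputs and vanishes if loss is equal and similar.

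About two maternal deaths per district could not support a comparison in any case, so that item matters more for honest reporting than for inference.

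All of this stands and limits the point. It does not remove it. The completion requirement and the replacement rule are written into the protocol, and they govern enrolment and data collection. A later analysis plan cannot recover outcomes that were not collected, and the document describes no end-of-intervention questionnaire for a woman who has been replaced.

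**Conclusion.** The point holds as a fault in a stated rule. The protocol sets a target of completers in both districts, replaces drop-outs without defining them, and places this rule over the window in which its mortality outcomes occur. As written it permits a completers-only comparison; it does not prove that one will be made, or that deaths will be removed.

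The document gives no drop-out rate and no contrast between women who stay and women who leave, so the bias has no computable size. Under the assumptions shown it runs from 0 with equal and similar loss to 5 points with 20% net excess non-completion and a 25-point gap, and the sign follows whichever district loses more. The second illustration reaches 7.4 points. Against a planned difference of 10 points, that range justifies correcting the rule while outcome data can still be collected.

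**What to change.** In section 2.9:
- Remove the requirement that 1218 women complete the interventions. The 10% allowance already provides for non-response.
- Define drop-out and reconcile it with the migration rule in section 2.4.
- State that maternal death, pregnancy loss, stillbirth and newborn death are outcomes and never drop-outs.
- Treat any further women enrolled as additions, not substitutes, and report their number by district.

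For the analysis, include every enrolled woman by district of enrolment whatever number of visits she received. Keep outcomes already observed in women who migrate or stop. Report a completers' analysis only as a labelled sensitivity analysis.

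This is mainly a change of wording. New routes of outcome collection, such as telephone or a relative, are not needed for it and might require further approval. The cost is that complete questionnaires may fall below 609 per district. At the planned 10% non-response, 609 × 0.90 = 548 would remain, close to the 1107 / 2 = 553.5 on which section 2.8 rests.
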